## Background

Suboptimal dietary pattern is a major contributing factor to the growing incidence of non-communicable diseases (NCDs) in China, which is characterized by a high intake of fat and sodium and a low intake of vegetables and fruits . The rapid modernization of the restaurant and packaged food industry has aggravated unhealthy dietary pattern . China has set a nationwide target to reduce the intake of dietary oil, salt, and sugar, as well as promoting nutrition education to help the public adopt healthier eating habits . However, recent data reveals that in comparison to the number of registered dietitians (RDs) and registered dietetic technicians (DTRs) in developed countries, China has a much lower ratio, with only 67 RDs/DTRs per 10 million people, which is far from meeting the massive needs of nutrition guidance .

PN (personalized nutrition) is a field that utilizes human individuality to develop nutrition approaches that prevent, manage, and treat diseases and optimize health . Previous studies have suggested that smartphones with built-in AI (artificial intelligence)-based algorithms are cost-effective, flexible, visually appealing and engaging, which could approach PN guidance and therapeutics provided by real healthcare professionals .

Substantial evidence indicates that randomized controlled trials (RCTs) hardly shift into real-world practice . In most long-term weight loss studies in humans, favorable results were achieved during the intervention but hard to keep after returning to normal life . In contrast, real world studies allow participants to follow their daily routines and enjoy real-life meals on wills, which might facilitate a trial becoming a real-world practice .

We have developed a PN approach with an AI-based smartphone applet, which aims to help provide the information of dish nutrition evaluation and PN evaluation after meal consumption for the mass of people under the circumstance of dietitian

shortage in China. This study is to identify the effectiveness and feasibility of this novel approach in a parallel, randomized, controlled trial in real world scenario.

## Methods

### Setting and study design

This trial is a two-arm parallel, randomized, controlled study in real-world situations. This smartphone applet with built-in AI-based algorithm only takes effect where dishes prepared by recipes with quantity (in China, same dish prepared at different home are different in cooking but dishes in central kitchen or food factory are prepared strictly following standard cooking procedure ). Participants are enrolled sequentially until the sample size reaches requirement. This study will be carried out in a pilot company employing 3000 people and food is prepared by the central kitchen at staff canteen. All participants will choose and consume meals on their own wills during the study. Weight and blood pressure measuring tools placed at the canteen can be available to participants; therefore, they can conveniently measure and record anthropometric indicators through the applet.

**Phase I.** The employees will be recruited to dine in the canteen for 3 months, assigned to the intervention or control group randomly. Both groups will be asked to use the applet to record their lunch each weekday during the study. After 1 week of run-in period, the intervention group will be able to access the information of dish nutrition evaluation and PN evaluation after meal consumption, while the control group will not. Both groups will be followed up by researchers on the same time schedules for the outcome measurements.

**Phase II.** Full-functioned applet will be available for use by all the diners (about 800) for another 1 year. Who use the applet at least 2 days per week will be regarded as the intervention group while the others will be the control group. During this phase, metabolic indicators from the annual physical examination will be provided by the company.

Figure 1 outlines the study design and Table 1 presents the visits and data

60 collection schedule.

61

62 Figure 1. Study design of the trial.

[figure not shown]

63

64

65 Table 1. Visits and data collection schedule

|                           | Phase I (3 months) |        |           | Phase II (1 year) |        |           |
|---------------------------|--------------------|--------|-----------|-------------------|--------|-----------|
|                           | Screening          | Run-in | Follow-up | Screening         | Run-in | Follow-up |
| Informed consent          | √                  |        |           | √                 |        |           |
| Questionnaire             |                    | √      | √         |                   | √      | √         |
| Dietary record            |                    | √      | √         |                   | √      | √         |
| Anthropometric indicators |                    | √      | √         |                   | √      | √         |
| Metabolic indicators      |                    |        |           |                   | √      | √         |

66

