### ***Recruitment and follow-up***

**Pilot.** To establish the feasibility and acceptability of current protocol, we recruited 94 employees to perform a 3-week, single-arm preliminary pilot trial and users tested this applet (data collection from February 2022 to March 2022).

**Phase I.** Recruitment and physical examination are planned to conduct at regular intervals during 3 months. Researchers ask employees about participation in the study, collect written informed consent from participants, instruct them to use the applet as well as measure their anthropometric indicators in a standardized way. Thereafter, participants complete demographic questions (birthdate, sex and occupation) through the applet, as well as answer questions regarding their family history of NCDs, physical fitness, drug use, physical activity level (PAL), sleep, smoking status, alcohol consumption, dietary habits and nutrition service needs. The follow-up questionnaire will be repeated at the end of the phase I and questions about user experience of this applet will be added to it.

**Phase II.** The intervention will last for another 1 year. All the diners will access the full-functioned applet. Metabolic data will be collected from the annual physical examination by the company. Participants will complete the same electronic questionnaire at pre- and post-intervention.

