### ***Randomization and blinding***

Following baseline measurements, the newly-enrolled participants will be randomized at a ratio of 1:1 to an intervention or control group. Randomization is stratified by sex and age. The trial is conducted as a double-blind study. The researchers are not blinded to allocation due to the nature of the intervention strategy, however the field investigators and participants will be blinded throughout the study, ensuring allocation concealment.

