## 218 **Outcomes**

219 In Phase I, dietary pattern, body weight or blood pressure optimizing is expected  
220 after the intervention. The primary outcome for the intervention effectiveness is  
221 dietary intakes. Anthropometric indicators including weight, body mass index (BMI),  
222 body composition and blood pressure are the secondary outcome. In Phase II, body  
223 metabolism normalization is expected after this period.

224

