## 233 **Statistical analysis**

234 The Mann-Kendall test will be implemented to examine the temporal trends of  
235 lunchtime food supply based on average “traffic light” score and animal/plant food  
236 ratio. For dietary record, we hypothesized that at least 5000 person-meal observations  
237 would be collected and analyzed over the follow-up period. Generalized linear mixed

models with intervention, time and 2-way interaction as fixed factors, will be used to examine the intervention effects on each outcome. A two-sided  $p$  value  $< 0.05$  will be considered to indicate statistical significance.

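### Phase II groups are formed by self-chosen applet use, so the metabolic comparison is observational and should not be reported as an intervention effect of a randomised trial

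*Protocol*

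**What the plan says.** The Protocol, under Setting and study design, introduces the study in one sentence: "This trial is a two-arm parallel, randomized, controlled study in real-world situations". For Phase I, employees are "assigned to the intervention or control group randomly". Randomization and blinding adds that "the newly-enrolled participants will be randomized at a ratio of 1:1 to an intervention or control group".

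Phase II is built differently. "Full-functioned applet will be available for use by all the diners (about 800) for another 1 year", and Recruitment and follow-up repeats it: "All the diners will access the full-functioned applet". Those who use the applet "at least 2 days per week will be regarded as the intervention group while the others will be the control group". The period over which the 2 days per week is judged is not given.

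Table 1 schedules metabolic indicators at the Phase II run-in and follow-up and at no Phase I visit. The values come from the company's annual examination. Outcomes says of Phase II that body "metabolism normalization is expected after this period". Statistical analysis makes no distinction between phases: generalised linear mixed "models with intervention, time and 2-way interaction as fixed factors, will be used to examine the intervention effects on each outcome".

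**The concern.** Phase I and Phase II share the labels intervention group and control group, the same model and the same randomised description, but the labels mean different things. In Phase I the groups differ by chance. In Phase II they differ because some diners chose to use a tool that all of them had. People who choose to log meals regularly may differ from others in how their metabolic health would have changed anyway.

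The metabolic conclusion is at stake. It comes only from Phase II, so no randomised metabolic comparison exists against which to check it. If the plan is run and reported as written, an association between use and metabolic change would appear as an intervention effect of a randomised controlled trial.

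**Working it through.** **1. Phase I and Phase II side by side**

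| Feature | Phase I | Phase II |
|---|---|---|
| Who gets the evaluation functions | Intervention group only, after run-in | All diners, about 800 |
| How groups are formed | Random, 1:1, stratified by sex and age | Own use, at least 2 days per week versus the rest |
| When membership is known | Before the functions are switched on | Only from use during the follow-up year |
| Metabolic indicators | Not scheduled | Run-in and follow-up |
| Stated model | Group, time, interaction | Group, time, interaction |

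The control group in Phase II has had nothing withheld. It can include former Phase I controls, occasional users and non-users.

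**2. What the interaction term does and does not remove**

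On the model scale, let the applet effect be δ. Let users and other diners have baseline levels b_U and b_O, and changes over the year unrelated to the applet of c_U and c_O.

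- Change in users: (b_U + c_U + δ) − b_U = c_U + δ.
- Change in others: (b_O + c_O) − b_O = c_O. For simplicity this treats occasional users as unexposed.
- Interaction = δ + (c_U − c_O).

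The baseline levels cancel. The term c_U − c_O does not. Under randomisation its expectation is zero; under self-selection nothing makes it so. Two plausible sources are:

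- exercise, alcohol or medication changing alongside applet use;
- regression to the mean among people who start using the applet after a poor examination.

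The documents give no figure for either.

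**3. The Phase II sample size**

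Sample size gives 20% metabolic syndrome after intervention and 200 per group, without a comparator rate or power. The figure can therefore only be solved backwards. With two-sided 5% and an assumed power of 80%,

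n = [z_α√(2p̄q̄) + z_β√(p₁q₁ + p₂q₂)]² / (p₂ − p₁)².

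Taking p₁ = 0.20 and p₂ = 0.323 gives [1.960 × 0.6215 + 0.842 × 0.6154]² / 0.123² ≈ 200. At an assumed 90% power the comparator would have to be about 34.4%. Either way the formula assumes groups alike apart from the applet, which the usage rule does not provide. Group sizes are also left to the diners: 200 in each group out of about 800 requires users to be between 200/800 = 25% and 600/800 = 75%.

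**4. An illustration, and its limit**

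Assume (not from the documents) no applet effect, 25% prevalence, half the diners regular users, and a correlation between motivation to use and lower metabolic-syndrome liability. At 200 versus 200:

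| Correlation | Users | Others | Rejection, post-only test | Rejection, group-by-time test |
|---|---|---|---|---|
| 0.1 | 22.5% | 27.5% | 22% | about 5% |
| 0.2 | 19.9% | 30.1% | 65% | about 5% |
| 0.3 | 17.3% | 32.7% | 95% | about 5% |

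For correlation 0.2, the post-only critical difference is 1.96 × √(0.25 × 0.75 × 2/200) = 0.085. The expected difference is 0.102 and its standard error is √[(0.199 × 0.801 + 0.301 × 0.699)/200] = 0.043. Power is Φ[(0.102 − 0.085)/0.043] ≈ 65%.

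The last column uses the logit scale and an assumed within-person residual correlation of 0.5 or 0.8. It stays near nominal because this scenario contains only stable imbalance (b_U ≠ b_O), which the interaction cancels. The post-only figures therefore apply only to an unadjusted comparison of year-end prevalence and do not measure the bias of the stated model.

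**The case against.** The protocol does not claim that Phase II is randomised. Random assignment is described for Phase I and for newly enrolled participants, and the usage rule is stated openly. The named primary outcome (dietary intakes) and the secondary outcomes (weight, BMI, body composition, blood pressure) belong to Phase I and are untouched. The stated model uses change from baseline, so it already handles stable differences. An SAP that is not shown may add covariates. All of this stands, and the absence of covariates from a short protocol summary is not a defect in itself. But adjustment reduces only measured confounding. It would not make the groups randomised, and the group definition is fixed in the protocol.

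Three stronger readings are tempting but not supported:

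- *A reader might infer that Phase II would produce false positives at the post-only rates above.* It would not under the stated interaction model, and no documented quantity measures the bias that remains.
- *A reader might infer that the bias must favour the applet.* Motivated loggers may start healthier, while people with a poor examination may take up the applet and start worse. The net direction cannot be known.
- *A reader might infer that leavers are counted as controls, or that the control group has no dietary data.* The protocol does not say how leavers are classed, and those who miss the follow-up examination may simply be missing. Diners using the applet less than 2 days per week do have some records, and the questionnaire covers dietary habits.

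**Conclusion.** The point holds for the status of Phase II. Its metabolic comparison is between self-selected groups, has no randomised counterpart, and is covered by the same randomised description and intervention-effects wording as Phase I. The bias that survives the stated model is c_U − c_O. Its size and sign are unknown from the documents, so no numerical false-positive rate is claimed for the planned analysis. The conclusion rests only on the protocol's group definition, its visit schedule and its model, not on the assumptions in the illustration. It should be corrected before Phase II is analysed or reported. Causal interpretation of Phase I is not affected by this point.

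**What to change.** - State that Phase II is an observational cohort of regular users versus other diners. Report its metabolic results as associations and limit causal claims to the randomised Phase I.
- State the period over which use of at least 2 days per week is assessed.
- Adjust the year-end metabolic comparison for its own baseline value and for variables already collected: sex, age, physical activity, smoking, alcohol, drug use and family history.
- Interpret between-group comparisons of applet-recorded diet with caution, because the amount recorded depends on the variable that defines the groups.
- Optionally, add a sensitivity analysis that fixes exposure in an early landmark window. Its drawback is that it misclassifies people who later start or stop, and it does not remove self-selection.

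The cost is protocol and analysis wording plus covariates already on the questionnaire; no new data collection is needed. Trial status says that the protocol was completed before any data were received and that Phase I field work was suspended, with later work still being arranged. The price is a more modest Phase II claim.

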## 67 Sample size

68 In Phase I, the planned sample size per group was determined as 70 to detect an  
 69 assumed intervention effect size of 0.25 in animal/plant food ratio over 4 months.  
 70 Statistical power was set at 90% with a significance level of 5%, using an SD in  
 71 animal/plant food ratio of 0.41 from the Shanghai Diet and Health Survey ,  
 72 considering a 15% dropout rate. In Phase II, assuming that the prevalence of

metabolic syndrome after intervention is approximately 20% based on the available research evidence, we would need 200 participants in each group to have sufficient power to detect the given effect size.

## **Procedure**

### ***Inclusion and exclusion criteria***

Men and women will be eligible to participate if they (1) are more than 18 years old, (2) are healthy in appearance, (3) promise to have lunch at the staff canteen during the study period, (4) agree to record food consumption of each meal on the applet. Exclusion criteria include: (1) planning to change physical activity habits during the course of study; (2) unable to follow a regular diet (e.g. on diet).

### ***Recruitment and follow-up***

**Pilot.** To establish the feasibility and acceptability of current protocol, we recruited 94 employees to perform a 3-week, single-arm preliminary pilot trial and users tested this applet (data collection from February 2022 to March 2022).

**Phase I.** Recruitment and physical examination are planned to conduct at regular intervals during 3 months. Researchers ask employees about participation in the study, collect written informed consent from participants, instruct them to use the applet as well as measure their anthropometric indicators in a standardized way. Thereafter, participants complete demographic questions (birthdate, sex and occupation) through the applet, as well as answer questions regarding their family history of NCDs, physical fitness, drug use, physical activity level (PAL), sleep, smoking status, alcohol consumption, dietary habits and nutrition service needs. The follow-up questionnaire will be repeated at the end of the phase I and questions about user experience of this applet will be added to it.

**Phase II.** The intervention will last for another 1 year. All the diners will access the full-functioned applet. Metabolic data will be collected from the annual physical examination by the company. Participants will complete the same electronic questionnaire at pre- and post-intervention.

### ***Randomization and blinding***

Following baseline measurements, the newly-enrolled participants will be randomized at a ratio of 1:1 to an intervention or control group. Randomization is stratified by sex and age. The trial is conducted as a double-blind study. The researchers are not blinded to allocation due to the nature of the intervention strategy, however the field investigators and participants will be blinded throughout the study, ensuring allocation concealment.

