 According to Chinese food composition database, energy[j] refers to content of energy in 100g edible portion of food item[j].

 According to Chinese food composition database, nutrient[j] refers to content of nutrient in 100g edible portion of food item[j].

The intervenors can browse and choose dishes on the ordering interface of the applet. Colored dots are displayed next to the dishes' names by a "traffic light" approach to indicate whether the dishes are benefit for health. The judgement of three colors is based on the contents of fat, sodium and sugar (green = reaching the dietary

recommendations, yellow = between the recommendations and average intakes among Chinese population , red = above the upper limit of intakes). The dietary recommendations in this study are: no more than 8g fat, 500mg sodium and 4.5g sugar in 100g dish (raw weight except for condiments). The cutoffs of nutrient contents according to the definition of “traffic lights” are listed in Table 2.

Table 2. The cutoffs of nutrient contents for dish nutrition evaluation

| Nutrient content               | I    | II       | III   |
|--------------------------------|------|----------|-------|
| Fat (g/100g  )     | <8   | 8-20     | >20   |
| Sodium (mg/100g  ) | <500 | 500-1000 | >1000 |
| Sugar (g/100g  )   | <4.5 | 4.5-9    | >9    |

 Green light for the dish represents all three indices within the range in the I column, red indicates at least 1 index within the range in the III column and yellow includes all the others.

 100g refers to 100g edible portion of dish.

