By comparison with recommended intake, the PN evaluation regarding actual intake will be provided for participants. The key evaluation indices for meal consumption are described in Table 3, including fat, sodium, meat and vegetables. For each index, we assign a health score with a corresponding mark to illustrate the comparisons between the current consumption and the national dietary recommendations. For example, a mark of three plus (+++) for fat indicates that the percentage of energy intake from fat is far from recommendation. Evaluation of fat and sodium is given greater weight than others, with a score of 0-3, because these two dietary factors are more related to burden of NCDs in China. Finally, an aggregate score of all the indices will be obtained, which represents the healthiness of whole meal consumption, 0 being the unhealthiest, and 10 being very healthy.

Table 3. The key evaluation indices for meal consumption

| Evaluation index                                    | Range  | Health score | Mark |
|-----------------------------------------------------|--------|--------------|------|
| Fat: percentage of energy intake from fat, % | <20    | 2            | —    |
|                                                     | 20-<30 | 3            | Good |
|                                                     | 30-<40 | 2            | +    |
|                                                     | 40-<50 | 1            | ++   |
|                                                     | 50-<60 | 0.5          | +++  |

|                                                    |            |     |      |
|----------------------------------------------------|------------|-----|------|
|                                                    | >60        | 0   | ++++ |
| Sodium: actual intake, mg                   | <1000      | 3   | Good |
|                                                    | 1000-<1400 | 2   | +    |
|                                                    | 1400-<1800 | 1   | ++   |
|                                                    | 1800-<2200 | 0.5 | +++  |
|                                                    | >2200      | 0   | ++++ |
| Meat: actual/recommended intake ratio       | <0.8       | 1   | —    |
|                                                    | 0.8-<1.2   | 2   | Good |
|                                                    | 1.2-<1.4   | 1   | +    |

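### Phase I is labelled double-blind, but only one arm sees the applet's evaluations, the primary outcome is self-recorded, and outcome follow-up is given to the role declared unblinded

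*Protocol*

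**What the plan says.** Under Randomization and blinding, the Protocol states "The trial is conducted as a double-blind study". It then separates two staff roles. On one side, "The researchers are not blinded to allocation due to the nature of the intervention strategy". On the other, "the field investigators and participants will be blinded throughout the study, ensuring allocation concealment". Randomisation is 1:1, stratified by sex and age, and takes place after baseline measurements.

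Under Setting and study design, both arms record weekday lunches in the applet. After a one-week run-in the arms diverge: "intervention group will be able to access the information of dish nutrition evaluation and PN evaluation after meal consumption, while the control group will not". Dish nutrition evaluation describes the first element as coloured dots beside dish names on the ordering screen. For the second element, the section on PN evaluation after meal consumption says that "the PN evaluation regarding actual intake will be provided for participants".

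On outcome assessment, Setting and study design says "Both groups will be followed up by researchers on the same time schedules for the outcome measurements". The Outcomes section makes dietary intakes primary, and weight, BMI, body composition and blood pressure secondary.

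**The concern.** The intervention is itself visible information, shown to one arm and withheld from the other. A participant whose screen changes after the run-in has received the intervention and can see it. The blinding claim for participants therefore conflicts with the description of the intervention.

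Two further statements compound this. The staff role named for outcome follow-up is the one declared unblinded. And blinding during the study is offered as the reason why allocation is concealed, although concealment concerns whether the person enrolling can foresee the next assignment.

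What is at stake is how far readers can trust the outcomes. A double-blind label tells them that differential reporting and assessor bias are controlled by design. Here the primary data are typed in by participants, and one arm is then graded on what it typed.

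**Working it through.** The point rests on comparing sections, not on a disputed figure.

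**1. Participants.** Randomization and blinding declares them blind throughout. Setting and study design gives the evaluations to one arm only, after a week in which neither arm had them. Both arms eat in the same company canteen. The Protocol describes no sham display, no matched control content and no step to keep participants unaware of their arm. The blinding claim cannot hold for participants.

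**2. Link to the primary outcome.** In the section on PN evaluation after meal consumption, intake per dish is the dish value × portions × (1 − discarded proportion), and the last two are entered by the participant. The same entries are then compared with recommendations for fat, sodium, meat and vegetables, and the evaluation is returned to the intervention arm. The meat and vegetable entries also feed the animal/plant food ratio used to size Phase I. Differential reporting does not require a participant to know the allocation list. Being graded on one's own entries is enough to create the motive.

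**3. Staff roles.**

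| Role | Declared status | Measuring tasks stated |
|---|---|---|
| Researchers | Not blinded | Follow-up of both arms for outcome measurements |
| Field investigators | Blinded | Weighing dishes and recipe materials (Dish nutrition evaluation) |
| Participants | Declared blinded | Portions and discarded share; can also measure and record anthropometric indicators at the canteen through the applet |

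No sentence gives the blinded staff any measurement of a participant.

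**4. Concealment.** Blinding acts after assignment and concealment acts before it, so the first cannot ensure the second. Randomising after baseline is stated and helps. It does not say whether the enrolling researcher can foresee the assignment.

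**5. Phase covered.** In Phase II all diners get the full applet and groups are defined by use, so the blinding statement can concern only Phase I.

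**6. The plan's own figure, for context.** Inputs from Sample size: difference 0.25, SD 0.41, power 90%, significance level 5%, dropout 15%; two-sided testing from Statistical analysis.

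- n per arm = 2(1.960 + 1.282)² × 0.41² / 0.25² ≈ 56.5, so 57
- 57 / 0.85 = 67.1, so 68. A t-test calculation gives 58, and 58 / 0.85 = 68.2, so 69. The stated 70 reproduces.

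**7. Sensitivity, on assumed values only.** With 70 × 0.85 = 59.5 completers per arm, SE = 0.41 × √(2/59.5) ≈ 0.075. Suppose there is no true effect but reporting differs between arms by b in the ratio. The two-sided false-positive rate is then 1 − Φ(1.96 − b/SE) + Φ(−1.96 − b/SE):

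| Assumed b | False-positive rate |
|---|---|
| 0 | 5% |
| 0.05 | about 10% |
| 0.10 | about 26% |
| 0.15 | about 51% |

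This treats each participant as contributing one ratio, as the sample-size calculation does, whereas the planned mixed model uses repeated meals. No value of b comes from the Protocol, and the conclusion does not depend on the table.

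**The case against.** The strongest reply is that participant unblinding is inherent in an information intervention and no redesign removes it. Sample size, randomisation and model all stay as they are, so this would be a matter of labelling and role description. That is largely right about the remedy for the primary outcome. It does not excuse a label that claims a protection the design lacks, and assessor blinding for the secondary outcomes can be improved.

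It can also be said that participants might not know that two versions of the applet exist. That is possible, but the Protocol describes no such step, and the grading of one arm's own entries would remain.

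A reader might infer more than the text supports, in four ways:

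- **That unblinded staff are shown to take the outcome readings.** The follow-up sentence names researchers but does not say who performs each measurement. Quality control uses the word loosely for everyone trained in data collection, and the authors may have meant field investigators to measure. The anthropometry mentioned under Recruitment and follow-up does not help: it is enrolment work, before any allocation exists, and its grammar could mean that participants are told to measure themselves.
- **That no blinding exists at all.** Nothing contradicts the blinding of field investigators, and the Protocol openly says that researchers are unblinded.
- **That participants see the 0 to 10 total.** The text says that the total is obtained and that an evaluation is provided. It does not say that the total is displayed, and the screen image is not available.
- **That allocation was in fact foreseeable.** The text gives a wrong reason for concealment, which does not show that concealment failed.

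**Conclusion.** The point holds in this form. The participant-blinding claim is contradicted by the Protocol's own description of the intervention, and it touches all of the Phase I primary outcome, because that outcome is computed from participants' entries. For the secondary outcomes, the only role named for follow-up is the unblinded one, and the blinded role has no stated task with participants, so blinded assessment is not established as written. The concealment phrase is an error of reasoning.

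The size of any bias is unknown. A reader might take the false-positive rates in the sensitivity table as estimates, but they follow from assumed shifts only. The conclusion assumes that no sham or masking procedure exists beyond what the Protocol describes.

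**What to change.** - Describe Phase I as open-label to participants. State that the self-recorded diet outcome is unblinded and open to differential reporting of unknown size.
- Assign post-randomisation weight, body composition and blood pressure measurement to the field investigators already declared blind, and use those readings for the secondary outcomes rather than readings that participants enter themselves.
- According to Trial status, recruitment began in September 2022 and Phase I field work was suspended in December 2022. Report separately any participants already measured another way before the suspension.
- Replace the concealment phrase with a statement that the stratified assignment is released only after enrolment and baseline are recorded and cannot be foreseen by the enrolling researcher.

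The cost is revised wording, a less favourable design label, and a task moved between staff roles. Measurer and method may change partway through Phase I, which is why the separate reporting is needed. Whether field investigators have the capacity to measure participants is not stated and has to be confirmed.
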